**Figure 1 F1:**
[figure not shown]
Study flowchart.

Patient screening and inclusion are performed at selected study centers according to the defined inclusion and exclusion criteria (see below). Standardized onboarding training, printed guides, and caregiver assistance documentation are provided for all study sites. The study centers hold cross-regional stroke units treating >1,000 patients with ischemic stroke or TIA per year and collaborate with cardiologists experienced in implantation of event-recorders. All patients included in the clinical study will receive standard of care for cryptogenic TIA/ischemic stroke. The study intervention consists of wearing a smartwatch (i.e., Scanwatch, Withings), which is CE-certified as medical device for AFib detection. Smartwatch- and Event Recorder-derived heart rhythm are daily uploaded and analyzed by cardiologists at the Cardiology Core Lab at the Department of Internal Medicine I, TUM Klinikum Rechts der Isar, Munich. Obtained data on cardiac arrhythmia will be accessible for each study site in consultation with the Cardiology Core Lab. In case of AFib detection (defined as arrhythmia lasting longer than 30 s), the including study site will be informed to set an *ad-hoc* detection visit and determine further therapeutic options. The study also includes a total of four pre-scheduled visits, to confirm eligibility, to record stroke and patient characteristics, smartwatch application and usability, stroke recurrence and adverse events (see Table 1). The baseline visit (Visit 0) may take place within the clinical setting of the acute stroke work up. The second and third visit (Visit 1, Visit 2) constitute phone-visits at 1 and 3 months. The last visit at the end of the study (Visit 3) will be performed at 6 months. In-patient visits will take place at each patient's study center.

**Table 1 T1:** Data to be collected.

**Data to be collected**	**Visit 0**	**Visit 1^¥^**	**Visit 2^¥^**	**Visit 3**	**Detection visit**
	**Max. 6 months after stroke/TIA**	**1 month** ±**1 week**	**3 months** ±**1 week**	**6 months** ±**3 weeks**^#^	**If AFib is confirmed**
In-/exclusion criteria^a^	X				
Patient characteristics^b^	X			X	
Stroke characteristics^c^	X				
Physical examination^d^	X			X	
NIHSS	X			X	
mRS	X	X	X	X	
Application of smartwatch^e^		X	X	X	
Stroke/TIA recurrency		X	X	X	
AESI/device incidents		X	X	X	
Detection of AFib^f^					X
Study termination				X	

^a^See methods.

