### Sample size estimation

2.4

According to a previous study a sensitivity and specificity for AFib detection per patient of >99 and 90%, can be assumed, respectively (18). Thus, 40 cases of AFib are required to estimate the sensitivity with a precision of about 10%, i.e., the difference of the lower bound of a two-sided exact 95% confidence interval and the point estimate of the sensitivity is 10%. As other studies observe paroxysmal AFib in 9%−16% of patients with cryptogenic stroke (4, 5), we intend to enroll 400 patients to obtain the required 40 cases. The specificity can consequently be measured with a precision of 4%. Our inclusion criteria should lead to a preselection of candidates with increased AFib risk factors. Therefore, AFib detection rate might increase up to 28% (max = 112) in our cohort within 6 months (8). The event of a 10% drop-out rate (e.g., due to withdrawal of consent, eligibility violations, no intervention, or non-existent data after inclusion into the study) would result in a minimum of 36 AFib cases and a similar precision of estimation i.e., 12% for the sensitivity and 4% for the specificity.

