### Statistical methods and analysis populations

2.5

Point estimates and two-sided exact 95% confidence intervals will be computed for the sensitivity and specificity referring to the primary objectives, related secondary objectives and subgroup analyses. Cardiologist-supervised event recorder-based continuous ECG rhythm analysis serves as the gold standard. Thus, in the case of discordant results, we consider the analysis of the signal from the event recorder by the cardiologist as the true status. As power calculation is based on participants with detected AFib as effective sample size (n_AFib_), we intend on analyzing our data as soon as one of the following situations occurs: (1) AFib is detected in 40 participants, who have completed follow-up or (2) enrolment and follow up is complete for all 400 participants (n_Enrolment_). In the first situation, the study leadership, the statistician, and the steering committee will decide on continuation of enrolment. Exploratory hypothesis testing of comparisons will be performed by McNemar's Chi-squared Test at two-sided 5% levels of significance. Due to the exploratory character of the analysis, and in accordance with the calculation of 95% confidence intervals, there will be no correction for multiple testing. With reference to the ICH E9 Guideline, the analyses will be performed using a full analysis set (FAS), according to the intention-to-treat principle (ITT), and a per protocol set (PP). The former will include all times with event recorder measurements (until possible but unexpected losses to follow-up) and the latter will include only times with additional smartwatch recordings. Therefore, missing values, possibly due to non-compliance, will be rated as no signal of an AFib by the smartwatch in the FAS. The FAS and PP analysis populations coincide when smartwatch records are available in all patients. Patients with eligibility violations (concerning inclusion or exclusion criteria), no intervention or non-existent data after inclusion into the study will be excluded from analysis. Time to confirmed AFib diagnosis, count of AFib diagnoses, AFib burden, safety endpoints and usability of smartwatches will be reported by descriptive statistics (mean, standard deviation, median, interquartile range, absolute and relative frequency). AFib risk factors will be compared between patient groups with and without AFib using descriptive statistics, hypothesis testing and multiple logistic regression models. Pre-defined subgroup analyses will be performed as described above.

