
## Discussion

3

Adequate work-up of cryptogenic stroke and especially AFib screening is highly relevant for secondary stroke prevention and risk reduction (1, 2). Naturally, probability of AFib detection correlates with duration and intensity of rhythm monitoring (4, 5). Prolonged AFib screening after stroke is currently suboptimal due to a limitation of resources, loss to follow-up, invasiveness of procedures, and costs.

Application of smartwatches has been shown to sufficiently detect paroxysmal AFib in the general population (14–16). As stroke patients often suffer from relevant disabilities, a transfer from existing data from otherwise healthy individuals cannot be assumed and prospective clinical research is urgently needed. We hence propose the prospective, multi-center clinical study “WATCH AFib” to assess the accuracy of smartwatches for AFib detection in stroke patients.

We choose an intraindividual control for AFib detection and use cardiologist supervised implanted event recorders as gold standard. This does (i) guarantee an accurate evaluation of the sensitivity and specificity and (ii) ensures that all participants receive appropriate diagnostics and subsequent anticoagulation therapy if indicated.

As the study intervention consists in simply wearing a smartwatch, as phone visits are implemented at 1 and 3 months, and as the time of follow-up (i.e., 6 months) is rather short, we expect a low rate of compliance issues or of loss to follow-up and estimate this to be around 5%−10%.

Inclusion criteria were specified for known AFib risk factors to increase detection rates and thus, study power (8). Therefore, the resulting cohort might be older and more diseased than the general stroke population. If smartwatches prove applicable for AFib detection in our cohort, results should be extendable to the general stroke population. In addition, we assess the accuracy of smartwatches in subgroups of patients with persisting neurological deficits or severely affected patients and include patients with authorized caregivers. For technical reasons, patients with pacemakers/defibrillators, patients without smartphones, and participants who cannot actively perform a one-lead ECG using the smartwatch need to be excluded.

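### Patients who never wear the watch can be dropped from the full analysis set even when the recorder shows AFib, so sensitivity can be biased upward

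*Protocol article*

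**What the plan says.** All references are to the protocol article.

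- **What the intervention is.** Section 2.1 (Study design): "The study intervention consists of wearing a smartwatch". The Discussion repeats it: "As the study intervention consists in simply wearing a smartwatch". Section 2.1 also says that the event recorder is not part of the study intervention.
- **Full analysis set.** Section 2.5 describes the FAS as "according to the intention-to-treat principle (ITT". On its content: "The former will include all times with event recorder measurements". On gaps in the watch record: "missing values, possibly due to non-compliance, will be rated as no signal of an AFib by the smartwatch in the FAS". The PP set keeps only times that also have watch recordings. The two sets are said to be the same when every patient has watch records.
- **Exclusion.** The next sentence of section 2.5 says that patients with eligibility violations, "no intervention or non-existent data after inclusion into the study will be excluded from analysis". It does not say from which set.
- **Drop-out.** Section 2.4 gives as examples of a 10% drop-out "withdrawal of consent, eligibility violations, no intervention, or non-existent data after inclusion into the study", and lowers the AFib cases from 40 to 36 accordingly.

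**The concern.** If the intervention is wearing the watch, a patient with no intervention is most naturally one who never wore it. That patient may still have a complete recorder trace. The missing-data rule would score such a patient, if AFib-positive on the recorder, as a miss. The exclusion rule removes the same patient. Someone who wears the watch for a day and is then missed counts against it, while someone who never puts it on does not count at all.

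Removal then depends on a failure of the index test while the reference result may exist. Dropping a recorder-positive never-wearer can only raise the estimated sensitivity or leave it unchanged. This affects the primary outcome and the two predefined subgroups (residual neurological deficit, and NIHSS of 8 or more). Section 2.2.2 defines those subgroups because watch usability might be impaired in them.

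**Working it through.** **Inputs.** From section 2.4: 40 AFib cases, 400 enrolled, assumed sensitivity above 99%, assumed specificity 90%, drop-out 10%. From section 2.5: two-sided exact 95% intervals. From the Discussion: 5% to 10% expected for compliance issues or loss to follow-up combined. The number of never-wearers, *k*, among recorder-positive patients is not given. It is an assumption here, shown as a range.

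**Interval.** Clopper-Pearson: the lower limit for *x* of *n* is the 2.5% quantile of Beta(*x*, *n* − *x* + 1). The upper limit is the 97.5% quantile of Beta(*x* + 1, *n* − *x*), or 1 if *x* = *n*.

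**Step 1: the plan's own figures.** Precision is the point estimate minus the lower limit.

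| Quantity | Estimate | Lower limit | Distance | Plan |
|---|---|---|---|---|
| Sensitivity, 39/40 | 97.5% | 86.8% | 10.7 | about 10% |
| Sensitivity, 35/36 | 97.2% | 85.5% | 11.8 | 12% |
| Specificity, 324/360 | 90.0% | 86.4% | 3.6 | 4% |
| Specificity, 292/324 | 90.1% | 86.3% | 3.8 | 4% |

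Case counts: 400 × 0.10 = 40 and 40 × 0.90 = 36. The planning figures reproduce.

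**Step 2: effect on sensitivity.** Let *s* be sensitivity in wearers.

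- Never-wearers excluded: estimate = *s*.
- Never-wearers scored as no signal: estimate = *s* × (40 − *k*)/40.
- Difference = *s* × *k*/40. Per patient this is 2.5 points at *s* = 1 and 2.4 points at *s* = 0.975.

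With every wearer detected:

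| *k* | Excluded (95% CI) | Kept, scored as missed (95% CI) |
|---|---|---|
| 1 | 39/39 = 100% (91.0 to 100) | 39/40 = 97.5% (86.8 to 99.9) |
| 2 | 38/38 = 100% (90.7 to 100) | 38/40 = 95.0% (83.1 to 99.4) |
| 4 | 36/36 = 100% (90.3 to 100) | 36/40 = 90.0% (76.3 to 97.2) |

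With one further miss among wearers at *k* = 4: 35/36 = 97.2% (85.5 to 99.9) against 35/40 = 87.5% (73.2 to 95.8).

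The row *k* = 4 is a ceiling. It takes the whole 10% drop-out (40 × 0.10 = 4) as never-wearers who still have recorder data.

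**Step 3: effect on specificity.** Take 400 − 40 = 360 AFib-free patients, specificity 90% in wearers, and a share *d* of never-wearers scored negative. Specificity = [0.90 × 360(1 − *d*) + 360*d*]/360.

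- *d* = 5%: (307.8 + 18)/360 = 90.5%.
- *d* = 10%: (291.6 + 36)/360 = 91.0%.

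Keeping never-wearers therefore raises specificity by 0.5 to 1.0 points over the 90% obtained when they are excluded.

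**The case against.** The strongest defence is that the two rules work at different levels. The FAS and PP definitions and the missing-data rule concern recording time, while the exclusion sentence concerns patients. One can first decide who is analysed and then score missing watch time as negative. On that reading there is no strict contradiction, and this much stands. The effect does not go away, because the patient-level step still removes complete non-use. The reading also sits poorly with the statement that FAS and PP coincide when all patients have watch records, which suggests that the FAS can hold patients without any.

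The wording also has milder readings. No intervention could mean that no watch was issued, and non-existent data could mean no recorder data. In the second case exclusion is unavoidable, because the true status is unknown. The article says neither, so these readings remain open.

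Other limits stand. Patients unable to record a one-lead ECG with the watch, or without a suitable smartphone, are excluded at entry (section 2.1.2), so complete non-use may be rare. Partial non-wear already counts against the watch in the FAS. Acceptance and practicability are exploratory objectives. Recorder upload is described as daily (section 2.1), but the article does not say that it goes ahead when the watch is never started.

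A reader might infer that sensitivity will be overstated by 10 points. The documents do not support that. Section 2.4's drop-out also covers withdrawn consent and eligibility violations, and the Discussion's 5% to 10% mixes compliance with loss to follow-up. Neither is a count of never-wearers.

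**Conclusion.** The point holds as a risk of bias created by a stated rule. The article fixes an exclusion that, on its most natural reading, removes complete failures of the index test from an analysis described as intention-to-treat. FAS sensitivity can then be biased upward, by about 2.5 points per recorder-positive never-wearer at 40 cases. The effect is zero if no such patient occurs. The ceiling is about 10 points, as large as the planned precision of 10% to 12%. The conclusion rests on three assumptions: that no intervention means never having worn the watch, that recorder data exist for these patients, and that at least one of them has AFib.

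It would go too far to say that the sensitivity is biased, or that the section flatly contradicts itself. The first depends on a count that is not given, and the time-versus-patient reading removes the second. The exclusion is nevertheless worth changing, because it bears on a primary measure and the other rules of the same section already supply the better treatment.

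**What to change.** In section 2.5, limit exclusions from the FAS to eligibility violations, withdrawn consent for data use, or no event-recorder data. Keep all other enrolled patients in the FAS, with absent watch data scored as no AFib signal for both sensitivity and specificity. Exclude never-wearers from the PP set only. In section 2.4, align the list of drop-out reasons, so that a never-wearer with recorder data no longer reduces the case count.

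The cost is a change to the exclusion sentence and a matching edit to the drop-out list. No new measurement is needed where recorder data are being transmitted. There are two downsides. Sensitivity may come out lower. Specificity will be slightly flattered, because AFib-free never-wearers become automatic true negatives (about 90.5% to 91.0% instead of 90% if 5% to 10% of them never wear the watch). FAS specificity should therefore be read alongside the PP result.

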
## Discussion

3

Adequate work-up of cryptogenic stroke and especially AFib screening is highly relevant for secondary stroke prevention and risk reduction (1, 2). Naturally, probability of AFib detection correlates with duration and intensity of rhythm monitoring (4, 5). Prolonged AFib screening after stroke is currently suboptimal due to a limitation of resources, loss to follow-up, invasiveness of procedures, and costs.

Application of smartwatches has been shown to sufficiently detect paroxysmal AFib in the general population (14–16). As stroke patients often suffer from relevant disabilities, a transfer from existing data from otherwise healthy individuals cannot be assumed and prospective clinical research is urgently needed. We hence propose the prospective, multi-center clinical study “WATCH AFib” to assess the accuracy of smartwatches for AFib detection in stroke patients.

We choose an intraindividual control for AFib detection and use cardiologist supervised implanted event recorders as gold standard. This does (i) guarantee an accurate evaluation of the sensitivity and specificity and (ii) ensures that all participants receive appropriate diagnostics and subsequent anticoagulation therapy if indicated.

As the study intervention consists in simply wearing a smartwatch, as phone visits are implemented at 1 and 3 months, and as the time of follow-up (i.e., 6 months) is rather short, we expect a low rate of compliance issues or of loss to follow-up and estimate this to be around 5%−10%.

Inclusion criteria were specified for known AFib risk factors to increase detection rates and thus, study power (8). Therefore, the resulting cohort might be older and more diseased than the general stroke population. If smartwatches prove applicable for AFib detection in our cohort, results should be extendable to the general stroke population. In addition, we assess the accuracy of smartwatches in subgroups of patients with persisting neurological deficits or severely affected patients and include patients with authorized caregivers. For technical reasons, patients with pacemakers/defibrillators, patients without smartphones, and participants who cannot actively perform a one-lead ECG using the smartwatch need to be excluded.

Naturally, our study shows some limitations and might face certain obstacles: First, as mentioned above we cannot include patients without smartphones or patients who are not able to actively perform a one-lead ECG. Second, recruitment might be challenging due to limited event recorder implantation in the general stroke population, due to the invasiveness and costs of the procedure. Nevertheless, validation of a new diagnostic tool should be done in comparison to the most accurate, available diagnostic test.

### Summary and conclusion

3.1

The current study prospectively validates accuracy of smartwatches for AFib detection in patients with cryptogenic stroke or TIA. Smartwatches might be a non-invasive, cost-effective, widely available alternative for prolonged rhythm monitoring, including implantable event recorders, and could potentially change the standard of post-stroke care.
